### Intervention

Intervention: New service pathway: A multi-component pathway comprising 3 parts:
Self-management kit: Immediately prior to hospital discharge patients will receive a written information pack from the research assistant (with verbal support at the time). Self-management programs are effective approaches in stroke management [21, 22] and are recommended in the Stroke Foundation Clinical Guidelines for Acute Stroke Management [3]. The kit will include written information about common difficulties specific to minor stroke, the need to see a General Practitioner (GP) after discharge from hospital for ongoing support, need for medications, referral to allied health services, and issues for the patient to discuss with their GP (via checklist). Participants will also receive the My Stroke Journey from the Stroke Foundation, which is a booklet available to all stroke patients in Australia about general stroke information.Customised screening checklist: To encourage patients to undertake self-management in collaboration with their GP, patients will be provided with a checklist to share with their GP. The checklist will include questions about services accessed and residual difficulties/changes post-stroke.Minor stroke sessional educational topics: Patients will be informed about a weekly program of minor stroke community-based educational topics delivered as a group program. These sessions will be facilitated by a qualified health professional and will be scheduled for 1.5 h weekly at rotating locations. Education sessions have been identified as a critical ingredient of successful self-management programs in chronic disease [23]. The group sessions will include brief information about common problems following minor stroke, return to work and driving, need for medications, issues to discuss with GPs, and will have a guest speaker from a different health discipline each time (e.g., physiotherapy, occupational therapy). Information will be “bite sized” (i.e., brief) [24] and patients will receive a short, written summary to take home. The final part of each session will be social, providing patients with a chance to discuss issues, build relationships and receive peer support. To improve adherence/attendance at the education sessions, participants will be sent a text reminder approximately 24 h before each session reminding them of the upcoming session.

The intervention will not be modified for participants in the new service pathway; however, participants will be able to participate in all or only come of the three new service pathway components. Participants’ use of each of the three components will be explored during the study evaluation. Participants in the new service pathway group will be able to receive usual care and referrals to health professionals at the hospital and in the community as individually indicated during the study.

### Outcomes

All participants will complete an initial face-to-face assessment. This will be repeated 1- and 3-months post-discharge. The research assistant administering the assessments will be blinded to participant randomisation group.

#### Primary outcome measure

Survey of Unmet Needs (SUNSU) [13]: Self-rating scale determining needs across impairment, activities of daily living, occupational activities, psychological needs, and community access. The SUNSU has 27-items (e.g., “Travelling in my community”). Participants tick beside an item if they are receiving help with that item and/or if they want help with that item. Each item is scored as “0” if participants do not receive/require help with that item, or “1” if participants require help with that item (therefore scores for each individual item range from “0” no help received or required for that item to “2” help received and required for that item). Higher scores represent more needs. The SUNSU has good person separation reliability and internal consistency scores [13].

#### Secondary outcome measures

Mayo-Portland Adaptability Inventory-4 (MPAI-4) [25]: A rating scale completed about ability, adjustment, and participation following acquired brain injury (including stroke). The individual version of the MPAI-4 will be used for the study. Each of the three scales (ability, adjustment, and participation) and the Full Scale MPAI-4 score are converted to T-scores (M = 50, SD = 10) to enable comparison with other adults with acquired brain injury [25]. The MPAI-4 performs well on measures of reliability and validity [25].Exeter Identity Transition Scales (EXITS) [26]: To record social group membership before and after stroke. The EXITS has four subscales to assess social group participation: 1) Group membership before the stroke; 2) Group membership after the stroke; 3) Maintenance of group membership post-stroke; and 4) New group memberships post. For each item, participants respond on a scale from 1 (Not at all true of me) to 7 (Completely true of me).Return to previous occupation (yes/no)RAND 36-Item Health Survey 1.0 (SF-36) [27]: Assesses subjective health and QOL across eight domains: physical functioning, pain, role limitations, emotional well-being, social functioning, energy, and perceptions about general health, and perceived change in health [28]. Items are scored from 0 to 100, with a higher score representing a more favourable state of health. The SF-36 performs well on measures of reliability, central tendency and variability (https://www.rand.org/health/surveys_tools/mos/36-item-short-form/scoring.html).Stroke Specific Quality of Life Scale (SSQOL) [29]: To measure of health-related QOL specific to stroke. The measure consists of 49 items categories into 12 domains: energy, family roles, language, mobility, mood, personality, self-care, social roles, thinking, upper extremity, vision, work and productivity. Participants score each on a score of 1 (“Total help – Couldn’t do it – Strongly agree”) to 5 (“No help needed – No trouble at all – Strongly disagree”) with reference to over the last week. The SSQOL performs well on measures of reliability and validity in mild and moderate stroke patients [29].Semi-structured interview regarding patients’ perceptions of the program: Approximately 25 intervention group patients will be purposively recruited for interview based on key dimensions (e.g. gender, age). Participants will be interviewed by a member of the research team in a mutually agreed location, with interviews lasting no longer than 45 min. Interviews will be audio recorded and transcribed for analysis.*Additional information:* Age, date of stroke, type of stroke, length of stay in hospital, health insurance status, highest level of education, occupation, living situation, and hospital readmissions.

### Data monitoring body

The study will be monitored through regular team meetings and quarterly meetings with the hospital stroke management team. Auditing will occur via the usual HREC auditing process.

### Statistical analysis

Data entry and coding will be undertaken by the research assistant who conducts each assessment session. Missing data will not be entered. Quantitative data will initially be analysed using descriptive analysis (counts, means, standard deviations where appropriate). Mixed model repeated measures will be used to analyse within and between group differences at discharge, and 1 and 3 months on the SUNSU, MPAI, EXITS, SF-36, SSQOL, number of services used, and hospital readmissions. Analyses will occur blinded to group allocation. Subgroup analyses will occur if required. Return to work outcomes will be analysed using Chi square tests. Semi-structured interviews will be analysed using qualitative content analysis [30]. It is not anticipated that interim analyses will occur.

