**Methods:**

One hundred ten patients with minor stroke will be recruited within a parallel, randomised controlled trial design comparing a new service pathway and usual care.

The new service pathway will comprise a self-management kit, customised General Practitioner checklist, and a series of minor stroke educational topics. Participants will complete assessments pre-hospital discharge and 1 and 3 months later. The primary outcome measure will be the Survey of Unmet Needs and Service Usage. Secondary outcome measures will include assessments of ability, adjustment and participation; social group connectedness; return to work; health-related quality of life; and perceptions of the new service pathway (intervention group only). Mixed model repeated measures will be used to analyse within and between group differences at each time point. Return to work will be analysed using Chi square tests. Perceptions of the new service pathway will be analysed qualitatively.

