### Sample size estimates

For a medium effect size (0.5) with 80% power for the 2 groups, 51 participants are required per group (calculated with G Power*2), increased to 55 to allow for dropout. Our previous project revealed that there were 2979 stroke admissions to the target hospital (Jan 2011-Jan 2017). Approximately 22% of stroke admissions met our inclusion criteria and were referred to our project, with 70% of eligible patients consenting to participate and being retained at follow-up.

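### The mixed model compares the groups at discharge, before the pathway can act, when the discharge score could be used to adjust the 1- and 3-month contrasts at no cost

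*Protocol article*

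**What the plan says.** The Statistical analysis section of the protocol article states: "Mixed model repeated measures will be used to analyse within and between group differences at discharge, and 1 and 3 months". The outcomes it then lists include the SUNSU, which is the primary measure. The Methods paragraph of the abstract says the same: "Mixed model repeated measures will be used to analyse within and between group differences at each time point".

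The baseline score exists for everyone. The Outcomes section says "All participants will complete an initial face-to-face assessment. This will be repeated 1- and 3-months post-discharge", and the abstract places the first assessment before discharge: "Participants will complete assessments pre-hospital discharge and 1 and 3 months later".

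The Primary aim and the Hypothesis concern unmet need at 1 and 3 months compared with usual care. Neither refers to a group difference at discharge.

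The article does not list the terms of the mixed model. It does not mention the discharge score as a covariate or a common discharge mean. The sample size rests on a standardised effect: "For a medium effect size (0.5) with 80% power for the 2 groups, 51 participants are required per group", "increased to 55 to allow for dropout". No significance level, sidedness or baseline correlation is given with it.

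**The concern.** Screening and recruitment take place in the last 24 hours of the hospital stay, and the first part of the pathway is handed over just before the patient leaves. The discharge assessment therefore measures unmet need before the pathway can have changed it. Any group difference found there is chance, and a between-group comparison at that visit does not bear on the aim.

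Listing discharge among the between-group comparisons also affects the other two visits. A model that yields a group difference at discharge must give each arm its own discharge mean. With complete data, the 1- and 3-month contrasts from that model are one of two things:

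- the raw difference between arms at the visit, which makes no use of the discharge score; or
- the difference in change from discharge, if the effect is read from the group-by-time term.

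Adjusting for the discharge score is at least as efficient as either. What is at stake is precision in a trial of 110 patients.

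The sentence also puts within-group differences beside between-group ones. Change within one arm mixes any effect of the pathway with the natural course after discharge, so it cannot stand as evidence of efficacy.

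**Working it through.** **Inputs.** From Sample size estimates: standardised effect d = 0.5, target power 80%, 51 analysed per group, 55 recruited per group. Assumed, because the article does not give them: the 5% significance level, shown both one-sided and two-sided; the correlation r between discharge and follow-up scores, shown from 0.1 to 0.6; and equal variance at discharge and follow-up. Power is for a single visit.

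**Step 1: the article's own figure.** For a two-sample t-test with n per group, the noncentrality is d × √(n/2) on 2n − 2 degrees of freedom. With n = 51 this is 0.5 × √25.5 = 2.525 on 100 degrees of freedom.

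- One-sided 5%: 51 per group is the smallest n that reaches 80% (power 80.6%). The stated figure is reproduced.
- Two-sided 5%: 64 per group would be needed, and 51 give 70.6%.

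**Step 2: effective effect size under each analysis.**

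- Raw contrast at a visit: d = 0.5.
- Adjusted for the discharge score: the residual variance shrinks by the factor 1 − r², so the effective effect is 0.5/√(1 − r²). At r = 0.3 this is 0.5/√0.91 = 0.524. At r = 0.5 it is 0.5/√0.75 = 0.577.
- Change from discharge: the variance is multiplied by 2(1 − r), so the effective effect is 0.5/√(2(1 − r)). At r = 0.3 this is 0.5/√1.4 = 0.423.

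The one degree of freedom spent on the covariate is ignored.

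**Step 3: power with 51 analysed per group.**

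| r | Raw, two-sided | Adjusted, two-sided | Change, two-sided | Raw, one-sided | Adjusted, one-sided | Change, one-sided |
|---|---|---|---|---|---|---|
| 0.1 | 70.6% | 71.0% | 46.2% | 80.6% | 80.9% | 58.9% |
| 0.2 | 70.6% | 72.3% | 50.7% | 80.6% | 82.0% | 63.2% |
| 0.3 | 70.6% | 74.6% | 56.1% | 80.6% | 83.7% | 68.2% |
| 0.4 | 70.6% | 77.9% | 62.7% | 80.6% | 86.2% | 74.0% |
| 0.5 | 70.6% | 82.3% | 70.6% | 80.6% | 89.4% | 80.6% |
| 0.6 | 70.6% | 87.8% | 79.8% | 80.6% | 93.2% | 87.7% |

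**Step 4: reading the table.** Adjustment has the highest power in every row. Against the raw contrast, the two-sided gain is 0.4 points at r = 0.1, 4.0 at r = 0.3, 11.7 at r = 0.5 and 17.2 at r = 0.6. Below r = 0.5 the change contrast does worse than the raw one, and at r = 0.3 it gives up 70.6 − 56.1 = 14.5 points. The adjusted analysis therefore gains little at low r, but it avoids the large loss that a change contrast would bring there.

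**The case against.** The article is condensed and lists no model terms, so a full analysis plan may already hold a baseline adjustment. Keeping discharge as a response visit is not wrong in itself, since a constrained longitudinal model does so too. Both statements stand, and the absence of a covariate is not the point here. The point is the stated between-group comparison at discharge. Neither a model with discharge as a covariate nor one with a common discharge mean would produce it, so adding the adjustment means changing that sentence.

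The correlation may be low. The Discussion says that difficulties may show themselves only once patients are home, and the SUNSU covers activities that an inpatient has not yet resumed. At r = 0.1 to 0.2 the gain over the raw contrast is only 0.4 to 1.7 points. This stands and limits the size of the claim. For the same reason, a chance imbalance at discharge would then carry over only weakly to follow-up.

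Several stronger readings are tempting, but the article does not support them:

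- **That the trial is under-sized and needs the adjustment to recover.** This presumes a two-sided test or losses above the allowance of 4/55 = 7.3%. The stated 51 is exactly the one-sided 5% answer, and the article states no sidedness.
- **That each visit is analysed on its own.** One mixed model spans the visits.
- **That a group effect averaged over all visits, diluted by discharge, is planned.** The text names each visit and mentions no average.
- **That both arms will improve, so that within-group tests will look like success.** The article does not say so. The Discussion suggests that needs may emerge after discharge, and the aims are comparative.

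**Conclusion.** The point holds as a matter of efficiency and clarity. The article plans a between-group comparison at a visit where randomisation already fixes the expected difference at zero. The free discharge means that this implies lead to follow-up contrasts no more efficient than an adjusted one.

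For r from 0.1 to 0.6, with d = 0.5 and 51 analysed per group, adjustment lifts two-sided power from 70.6% to between 71.0% and 87.8%, and one-sided power from 80.6% to between 80.9% and 93.2%. The size rests on an assumed r. The direction does not: adjustment is at no disadvantage anywhere in the range, whichever sidedness was meant. The equivalence to raw or change contrasts is exact for complete data; with missing visits the mixed model's contrasts would differ somewhat.

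A reader might infer that the planned analysis is biased or invalid. It is not: unadjusted contrasts in a randomised comparison remain valid.

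**What to change.** Revise the sentence in Statistical analysis, and its counterpart in the abstract, as follows.

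1. Estimate the between-group contrasts at both 1 and 3 months adjusted for the discharge score. One way is to use follow-up scores as responses, with group, visit, group-by-visit, discharge score and discharge-score-by-visit terms. The other is a constrained longitudinal model in which the two arms share one discharge mean.
2. Report discharge values by arm descriptively, without a between-group test.
3. State that conclusions about efficacy rest on the between-group contrasts, and that within-group changes are descriptive.

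Both follow-up visits should stay, because the Primary aim and the Hypothesis name both. Restricting the effect to 3 months is not needed here and would drop a stated comparison.

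The cost is a sentence or two in the analysis section, with no new data, visits or participants. Stating the significance level and sidedness in the same edit would settle which power columns apply.

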### Screening and randomisation

In the 24 h prior to hospital discharge, patients will be screened for eligibility and recruited. The recruitment strategy will involve a two-stream approach over an approximately 6-month period. In the first stream, potential participants will be identified by the stroke team. The second stream will involve pre-screening for potential participants using PowerTrials. Following potential participant identification, a member of the stroke team or a research assistant will approach all eligible people with minor stroke admitted to the recruiting hospital, thus allowing a fair recruitment strategy. Participants will be randomly allocated to receive usual care or the new service pathway. Randomisation will occur using a computerised random number generator (by the primary researcher) with 50:50 assignment to the new pathway or usual care (*N* = 55 participants per group). Assignment will be concealed using opaque envelopes. The participants and their families and the research assistant conducting the assessment sessions will be blinded to the intervention assignment. No circumstances are foreseen which will necessitate unblinding; however, if unblinding is required, the unblinding process for an individual participant will be conducted by the primary researcher.

Participants will consent to participate in the project using a written Participant Information and Consent Form (PICF). PICFs will be provided to potential participants by a member of the stroke team or research assistant. Potential participants will be informed that participation in the trial is entirely voluntary and that they can opt out of the trial.

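### Hospital readmissions are put in the rating-scale mixed model at three visits, although at the discharge visit they can only be zero (minor)

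*Protocol article*

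**What the plan says.** The Statistical analysis section of the protocol article states: "Mixed model repeated measures will be used to analyse within and between group differences at discharge, and 1 and 3 months on the SUNSU", and the same sentence goes on to "MPAI, EXITS, SF-36, SSQOL, number of services used, and hospital readmissions". All these outcomes share the same three time points. No error distribution, link or covariance structure is given. The section then treats one outcome separately: "Return to work outcomes will be analysed using Chi square tests".

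Readmissions are not among the secondary aims. Under Secondary outcome measures they close the list of additional information: "occupation, living situation, and hospital readmissions". The article does not say whether they are recorded as a count or as yes/no, and it gives no expected rate.

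On timing, the Abstract places the first assessment before hospital discharge, and Screening and randomisation places recruitment in the last 24 hours of the stay.

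**The concern.** A linear mixed model suits scale scores. Readmission differs in two ways.

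First, it is defined only after discharge from the index stay, so the first of the three modelled visits has no information and no variance. This needs no assumption about how often readmission occurs.

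Second, if events are few, the normal approximation for a difference in means becomes poor at about 50 patients per arm.

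The section commits to between-group inference on this outcome, so a test and an interval will be reported. At stake is a spuriously significant difference in readmissions, or an interval that covers less than stated, on one of the few outcomes here that is not a rating scale.

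**Working it through.** **1. Sample size used as input.** Sample size estimates states: "For a medium effect size (0.5) with 80% power for the 2 groups, 51 participants are required per group", "increased to 55 to allow for dropout". Alpha and sidedness are not stated. A one-sided t-test at an assumed 5% level with d = 0.5 gives 51 per group (power 80.6%); a two-sided test would need 64. The dropout step implies (55 − 51)/55 = 7.3%. Here 51 per arm serves only as the analysed number, with 1:1 allocation.

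**2. One variance shared over the three visits.** Let v1 and v3 be the true variances at 1 and 3 months; the variance at discharge is 0. The model uses v̄ = (0 + v1 + v3)/3 where v3 is needed. The standard error of the 3-month contrast is therefore multiplied by √(v̄/v3), and

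type I error ≈ 2[1 − Φ(1.96·√(v̄/v3))].

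| v1/v3 | v̄/v3 | SE factor | Type I error |
|---|---|---|---|
| 1/2 | 0.500 | 0.707 | 16.6% |
| 1/3 | 0.444 | 0.667 | 19.1% |
| 1/5 | 0.400 | 0.632 | 21.5% |

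At a constant low rate, variance is roughly proportional to the mean. A ratio of 1/2 then corresponds to counting events since the last visit (one month, then two), and 1/3 to cumulative counts. If early events made the two follow-up variances equal, v̄/v3 = 0.667, the factor is 0.816 and the type I error is still about 11%.

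Simulation agrees (20,000 null trials per setting, 51 per arm, Poisson or gamma-overdispersed counts, assumed 3-month means 0.03 to 0.20). Type I error was 16 to 18% with the 1-month mean at half the 3-month mean, and 19 to 21% with it at one third.

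**3. A separate variance for each visit.** The discharge row and column of an unstructured covariance matrix are zero, so the matrix is singular and the model cannot be fitted as written. The analyst has to drop the visit. A log or logit link does not help, because an all-zero visit has no finite estimate on that scale.

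**4. Discharge dropped, visit-specific variance.** With complete data the contrast is then the ordinary t contrast at that visit. Results at 51 per arm:

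| Assumed control mean | Type I error | Coverage at true ratio 0.5 |
|---|---|---|
| 0.03 | 2.5% | 88.6–88.7% |
| 0.05 | 3.6–4.2% | 90.2–90.8% |
| 0.10–0.20 | 3.9–4.7% | 94.5–95.5% |

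At a mean of 0.03 with ratio 0.5, the chance of no event in either arm is exp(−51 × (0.03 + 0.015)) = exp(−2.295) = 10.1%. Such a trial has no usable standard error and counts as a miss, which explains most of the shortfall at that mean. Under the null the chance is exp(−51 × 0.06) = 4.7%.

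**5. Number of services used.** With assumed means of 2 or 5, Poisson or overdispersed, at 51 per arm with visit-specific variance, type I error was 4.7 to 5.1% and coverage 94.6 to 95.3%.

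**The case against.** The strongest reply is that the article fixes neither a covariance structure nor a normal error distribution. A fuller plan, not shown, could specify both, and with visit-specific variances and a mean of 0.10 or more the 3-month test is near nominal. This stands as a limit on the size of the error: the 17 to 22% applies only to a shared variance. It does not remove the problem, because the sentence includes the discharge visit, and neither a visit-specific covariance nor a generalised model can use a visit at which every value is zero.

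Three stronger readings are tempting, and the documents do not support them.

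- A reader might infer that readmissions are known to be rare. The article gives no rate, so low means are an assumption and are shown as a range.
- A reader might infer that both count outcomes are wrongly analysed. For number of services used, the tests and intervals are close to nominal at this sample size, so a count model there is a preference.
- A reader might object to confidence limits below zero readmissions. That affects intervals for a single arm's mean. The planned comparison between arms is a difference, which may properly be negative.

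It is also fair to say that readmissions matter little to the trial's conclusions: they are listed beside background variables, are absent from the aims and play no part in the sample size. That sets the severity.

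**Conclusion.** The point holds for hospital readmissions only, and it is minor. As written, the analysis either shares a variance with an all-zero visit, giving about 17 to 22% false positives at 3 months against 5%, or is degenerate.

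The percentages rest on 51 analysed per arm, complete data, 3-month means of 0.03 to 0.20 and a 1-month variance between one half and one fifth of the 3-month variance. None of these readmission figures comes from the article. The zero at discharge rests on no such assumption.

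Once discharge is dropped and variances are visit-specific, what remains is a small-numbers problem. It is visible at means of 0.05 or less and essentially gone at 0.10 or more.

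**What to change.** Take hospital readmissions out of the mixed-model list and add a sentence such as: *The proportion of participants with at least one hospital readmission by 3 months after discharge (and by 1 month, if wanted) will be compared between arms as a risk difference with an exact or score 95% confidence interval; repeat readmissions will be tabulated by arm.* The sentence should also say how participants without a 3-month assessment are counted.

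This changes analysis wording only; no new data are needed and the sample size is unaffected. The small downside is that repeat readmissions are described and not tested.

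Number of services used may stay in the mixed model. A count model or robust standard errors for it is optional.
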